### Setting and recruiting

*Experimental group (EME, outpatient version 2023, plus standard care):* persons with long COVID-related fatigue following EME (revised edition 2023) in an outpatient setting at USZ, INSEL or REHAB, as part of their clinical routine and standard care, will be informed about this ongoing research and will be kindly asked if they are willing to participate in this project. If individuals agree, have signed the consent form and meet the inclusion/exclusion criteria checked by the study therapist on site, they will be included in the experimental group (EG). In these three public institutions, a group of trained OTs leads continuously EME groups and has received up-to-date training for the EME version 2023 in Spring 2024.

*CG (standard care*): a register of potential CG participants will be created through a contact with the Altea Network for Long COVID Association (ALTEA) and the patient organisation Long Covid Switzerland (LCS), both of which are partners in the study project and have been involved since the design phase. Using the contacts of ALTEA, LCS and specialised healthcare providers, information about the study will be disseminated, allowing interested persons to register themselves through a public link or QR code and to participate in a first online survey. Registration for the study has been open since 15 July 2024 and will remain open until summer 2025. Thereafter, based on the sociodemographic characteristics and clinical history of COVID-19, the CG participants will be selected from the register by their propensity score (PS) and matched with EG participants. Subsequently, the selected persons from the CG will be screened for eligibility, asked for their informed consent and included in the study.

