Outcomes	Impact of fatigue on physical, mental and social activities of daily routines measured by the Modified Fatigue Impact Scale Self-efficacy in performing energy management strategies measured using the Self-Efficacy for Performing Energy Conservation Strategies Assessment Perceived competency to perform 21 daily tasks measured by the Occupational Self-Assessment Health-related quality of life using the Short-Form 12 Item Health-Related Quality of Life Survey Description of the stable use of energy management strategies in daily life using the Behavioural Changes in Energy Management Survey Cost-effectiveness profile of the EME intervention plus the standard care vs standard care only: a self-reported questionnaire about disease-related and productivity costs
Interventions to be compared	Standard care: any interventions tailored to the personalised needs and goals of persons with long COVID Standard care plus occupatinal therapist-EME-group participation
Causal contrast	Per-protocol effect
Analysis plan	Each participant in the EG will be matched (1:1 ratio) to a participant in the CG by applying the optimal matching method using propensity score as a distance measure Outcomes will be analysed using an adjusted repeated measures mixed-effects linear regression model Cost-effectiveness by performing an economic evaluation

To emulate random assignment, each participant in the EG will be prospectively matched to a participant in the register according to their baseline sociodemographic characteristics (sex and age) and clinical history of long-COVID-related fatigue. We will choose 1:1 optimal matching using PS as a distance measure. We will employ a prospective matched design to compare outcomes between the experimental group and CGs. This ensures that CG participants are carefully selected in real time, concurrently with the enrolment of EG participants, to maximise group comparability and reduce confounding. For every 15 participants who are enrolled in the EG, we will prospectively match one CG participant to each EG participant. Optimal matching minimises the overall sum of pair-wise distances between treatment subjects and matched control subjects and is recommended when matching for the purpose of selecting well-matched controls for follow-up (eg, when the outcome values are not yet available).^39^

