Descriptive statistics will be used for all outcome measures at each measurement time to summarise results. To ensure that PS matching adequately balances measured confounders, we will carefully assess and report standardised differences between treatment groups before and after matching.^40^ Standardised differences are widely used because they are unaffected by sample size and provide a consistent measure of imbalance. A standardised difference of less than 10% (0.1 in absolute value) will be considered indicative of a clinically relevant balance between groups. Variables with standardised differences of greater than 10% will be flagged for potential residual confounding and addressed in sensitivity analyses.

Our causal contrast of interest will be the per-protocol effect, so to analyse the effect of adding EME to the standard care on the dependent continuous variables for both primary and secondary outcomes, an adjusted repeated measures mixed-effects linear regression model will be used. In addition to the covariates already included in the matching phase, we are aiming to include additional potential covariates related to the clinical history of long-COVID (eg, fatigue intensity, fatigue impact) and socio-demographic data (eg, education, occupation status).

Using PS matching combined with regression methods is a robust approach to account for measured confounding. However, this approach does not address unmeasured confounding, which could bias the results. To acknowledge this limitation and mitigate its impact, we will perform a sensitivity analysis to evaluate the robustness of your findings to potential unmeasured confounding. We will perform a simulated bias analysis to estimate the potential impact of unmeasured confounding. We will specify plausible distributions for an unmeasured confounder and assess its potential effect on the treatment-outcome relationship.^41^ In addition, we plan to conduct an E-value analysis for assessing whether our results are likely robust even in the presence of unmeasured confounders.^42^ The E-value quantifies the minimum strength of association that an unmeasured confounder would need to have with both the treatment and the outcome (beyond measured confounders) to explain away the observed treatment effect.^43^

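### Baseline variables flagged for imbalance above 0.1 go only to sensitivity analyses, so any flagged variable outside the primary model stays unadjusted in the main estimate

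*Protocol article*

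**What the plan says.** All places are in the protocol article.

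- **Matching** (Statistical analysis). Experimental group (EG) participants are matched to register members "according to their baseline sociodemographic characteristics (sex and age) and clinical history of long-COVID-related fatigue". The method is stated as "We will choose 1:1 optimal matching using PS as a distance measure", and it is run in batches: "For every 15 participants who are enrolled in the EG, we will prospectively match one CG participant to each EG participant".
- **Balance check** (Statistical analysis). "A standardised difference of less than 10% (0.1 in absolute value) will be considered indicative of a clinically relevant balance between groups". The response to a larger value is "Variables with standardised differences of greater than 10% will be flagged for potential residual confounding and addressed in sensitivity analyses". The section describes no re-match and no re-specification of the propensity model, and it does not move a flagged variable into the primary model.
- **Primary model** (Statistical analysis). An adjusted repeated measures mixed model contains the matching covariates. Further covariates (fatigue intensity, fatigue impact, education and occupation status are the examples) are described as something the authors aim to include.
- **Order of events** (Setting and recruiting; Table 2). People join the register by a process "allowing interested persons to register themselves through a public link or QR code and to participate in a first online survey". Matching is at week -2. After it, "Subsequently, the selected persons from the CG will be screened for eligibility, asked for their informed consent and included in the study". In the control group (CG), MFIS and SEPECSA first appear at T0 (week 0).

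**The concern.** Matching is the step meant to stand in for random assignment. A measured baseline variable known to differ between the groups is a known source of confounding if it also predicts the outcome. Under the stated rule, such a variable is dealt with only beside the main result. If it is also outside the primary model, the headline estimate carries the imbalance, and a reader has to find the correction in a secondary table. The rule will be triggered often, so what it prescribes matters.

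Matching also comes before control-group consent and before any T0 outcome. The study could therefore respond to poor balance without seeing outcome data, and the article does not provide for this.

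**Working it through.** **1. The plan's own figure (Sample size).** Difference 1.5, SD 2.2, 90% power, alpha 0.05 (two-sided), 24% loss:

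- n per arm = 2 × (1.960 + 1.282)² × 2.2² / 1.5² = 45.2, so 46.
- 46 / 0.76 = 60.5, so 61 per arm and 122 in total. This reproduces the plan. Nothing below changes it.

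**2. How often 0.1 is exceeded by chance.** The SE of a standardised difference is about √(2/n), and P = 2 × [1 − Φ(0.1/SE)] under randomisation:

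| n per arm | SE | P for one covariate |
|---|---|---|
| 15 | 0.365 | 78% |
| 46 | 0.209 | 63% |
| 61 | 0.181 | 58% |

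For six independent covariates at 61 per arm, P(at least one above 0.1) = 1 − 0.42⁶ = 99.5%, and the largest difference averages about 0.30.

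**3. What block matching leaves.** The article does not give the register size, the number of matching covariates or the shift between groups, so all are assumed here. The matching was simulated as optimal propensity score matching in blocks of about 15.

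- Four covariates, shift 0.2 to 0.4 SD, register 100 to 300: 86% to 99% of simulated trials had at least one difference above 0.1.
- Six covariates (two binary), shift 0.3 SD, register 200: 93% of runs, with an average largest difference of 0.18. On the same footing, this is better balanced than the randomised reference in step 2 (99.5%, 0.30).

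**4. Effect on the estimate.** For one variable left out of the model and unrelated to those in it, bias ≈ SMD × r × 2.2, where r is its correlation with the outcome (assumed 0.3 to 0.5):

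| SMD | Bias in points (r = 0.3 to 0.5) | Share of 1.5 |
|---|---|---|
| 0.1 | 0.07 to 0.11 | 4% to 7% |
| 0.2 | 0.13 to 0.22 | 9% to 15% |
| 0.3 | 0.20 to 0.33 | 13% to 22% |

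Simulated bias, with linear covariate effects:

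- Four-covariate simulation of step 3: 0.03 to 0.29 points unadjusted, and −0.02 to 0.01 (zero within simulation error) with all matching covariates in the model.
- Six covariates, three omitted from the outcome model: 0.09 to 0.26 points with a register of 100 (6% to 17% of 1.5), and up to 0.14 with a register of 200 (9%).
- Six covariates, all in the model: about zero, with or without re-matching.

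**5. What outcome-blind re-matching adds.** The best of 25 candidate matches per block was chosen on cumulative balance. Runs with any difference above 0.1, at a shift of 0.3 SD:

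- Register 200: from 90–98% down to 16–20% across repeated simulations.
- Register 300: from 91–93% down to 3%.
- Register 100: from 97–99% down to only 83–86%.

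With a 0.5 SD shift, 57% to 100% of runs still breached after re-matching. Re-matching improved the balance table. It gave no gain in the fully and linearly adjusted estimate.

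**The case against.** **The primary model already adjusts.** A reader might infer that, because the match is not repeated, avoidable confounding stays in the primary estimate. The documents do not support that for the matching covariates: they are in the primary model, and step 4 shows bias of about zero when their effects are linear. This objection stands and narrows the point to variables outside the model, non-linear effects and poor overlap.

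**Missing 0.1 is normal at this size.** This also stands. A reader might set a 93% breach rate for any of six covariates against 58% for one covariate under randomisation and conclude that the matching is poor. The like-for-like reference is 99.5%. The article uses 0.1 as an indicator and a flag, not as a condition for accepting a match.

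**Iteration may be described elsewhere.** The article does not exclude refining the propensity model, and a fuller plan may do so. This is fair for the re-matching step, which is therefore only a secondary suggestion. It does not cover the flagging rule, which the article states explicitly and which names sensitivity analyses as the response.

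**Re-matching has limits.** It can balance only what the register holds. MFIS and SEPECSA are first measured in controls at T0, so they are out of reach. Screening failures, refusals and the 24% loss can also undo balance after the match.

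**Controls are not strangers to the study.** It is tempting to say that they have not been contacted when matching is run. In fact they have consented to the register and completed a survey. They have only not yet been screened or consented for the control group.

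**Conclusion.** The point holds in a limited form. The stated rule leaves a flagged baseline variable out of the primary adjustment unless it happens to be in the model already, and inclusion of the non-matching covariates is only an aim. The plausible size is modest: 0.09 to 0.26 points with a register of 100 and up to 0.14 with 200, against a target of 1.5. These figures assume linear effects, three of six covariates omitted, and assumed group shifts and covariate–outcome associations. Non-linear effects and poor overlap could add to this and were not quantified. The check does not show that the matching method is faulty, that a breach of 0.1 signals failure, or that re-matching would change a fully adjusted estimate whose covariate effects are linear. It is worth changing because the remedy costs almost nothing.

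**What to change.** Replace the rule with:

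> Any measured baseline variable with an absolute standardised difference above 0.1, computed cumulatively over all pairs and again for participants analysed at T2, enters the primary outcome model; the model without these variables is the sensitivity analysis.

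This also covers T0 values of MFIS and SEPECSA, which matching cannot reach.

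As a secondary step, at each remaining block and before the selected persons are screened and consented for the control group, check cumulative balance on the register variables. If it is poor, re-specify the propensity model or re-match without outcome data. According to Project status, one block of 15 pairs had been matched by December 2024. That leaves 61 − 15 = 46 pairs, or about three blocks, in which earlier imbalance could be offset. The benefit depends on register size and group shift, which the article does not give.

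Cost: a few more covariates in the model and a few statistician hours per block. The total stays at 122.

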### Data collection

All questionnaires and surveys will be available in the three national languages (German, French and Italian) for both groups and at all time points online via Redcap (http://www.project-redcap.org/). If preferred, they will also be available on paper, either delivered personally by the local investigator or sent by post. Self-reported questionnaires documenting the outcomes of interest will be collected at different time points. In tables2  3, all procedures and data collection time points involving the CG and the EG are listed, respectively.

**Table 2 T2:** Register and control group: timeline of contacts and assessments

Timeline contacts	Register	Study period control group (CG)						
	Enrolment		T0		T1		T2	T3
Weeks	>14	-2	0	4	6	9	14	24
Information about register and study procedures	x							
Informed consent for register	x							
Sociodemographic characteristics	x							
Clinical history of (post-)COVID-19-condition	x						x	x
Matching		x						
Check study inclusion/exclusion criteria		x						
Informed consent for CG participation		x						
Outcomes								
MFIS			x		x		x	x
SEPECSA			x		x		x	x
OSA			x		x		x	x
SF-12			x		x		x	x
BCEM-S								x
Disease-related costs				x		x	x	x

BCEM-SBehavioural Changes in Energy Management SurveyMFISModified Fatigue Impact ScaleOSAOccupational Self-AssessmentSEPECSASelf-Efficacy for Performing Energy Conservation Strategies AssessmentSF-12Short-Form 12 items

**Table 3 T3:** Experimental group: timeline of contacts, assessments and energy management education intervention

Timeline contacts	Study period experimental group (eg,)							
	Enrolment		T0		T1		T2	T3
Weeks	>14	-2	0	4	6	9	14	24
Announced to EME at USZ, REHAB, INSEL		x						
Screening and inclusion into EME		x						
Written information about the study		x						
Check study inclusion/exclusion criteria			x					
Informed consent			x					
Sociodemographic characteristics			x					
Clinical history of (post-)COVID-19-condition			x				x	x
EME intervention (lessons 1–8)			L1-2-3-4-5-6-7-------8					
Outcomes								
MFIS			x		x		x	x
SEPECSA			x		x		x	x
OSA			x		x		x	x
SF-12			x		x		x	x
BCEM-S								x
Disease-related costs				x		x	x	x

BCEM-SBehavioural Changes in Energy Management SurveyEMEenergy management educationMFISModified Fatigue Impact ScaleOSAOccupational Self-AssessmentSEPECSASelf-Efficacy for Performing Energy Conservation Strategies AssessmentSF-12Short-Form 12 itemsUSZUniversity Hospital Zürich

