### Statistical methods and analysis

#### Sample size

The target study population are people with post-COVID-19 condition living in Switzerland. To calculate the sample size of this study, we used data from two previous studies. In the feasibility study with persons with long COVID-related fatigue, the mean difference of the primary outcome (self-efficacy in performing energy conservation strategies) at T2 (post-intervention) was 1.9 (95% CI: 2.89 to 0.90).^23^ We hypothesised, therefore, a difference of 1.5 points at T2 and conservative assumption of a SD of 2.2 points.^38^ Including a follow-up rate of 24% at T2, the estimated sample size to detect a difference of 1.5 points with 90% power (0.05 alpha) is 122 persons. Therefore, we aim at a total of 122 persons included in the study (eg, 61 and CG: 61).

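### The plan does not fix how baseline self-efficacy enters the week-14 comparison and schedules no baseline cost measure, so baseline differences between non-randomised groups may bias both results

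*Protocol article*

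**What the plan says.** **Powered outcome.** The Sample size section rests on self-efficacy (SEPECSA) after the intervention. It cites a feasibility study in which "the mean difference of the primary outcome (self-efficacy in performing energy conservation strategies) at T2 (post-intervention) was 1.9", and then assumes "a difference of 1.5 points at T2 and conservative assumption of a SD of 2.2 points".

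**Matching.** Each EME participant is "prospectively matched to a participant in the register according to their baseline sociodemographic characteristics (sex and age) and clinical history of long-COVID-related fatigue". Table 2 puts matching at week -2 and the first SEPECSA at T0 (week 0).

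**Adjustment.** The Statistical analysis section keeps the matching covariates in an adjusted mixed-effects linear model for repeated measures. Beyond these, "we are aiming to include additional potential covariates related to the clinical history of long-COVID (eg, fatigue intensity, fatigue impact"; education and occupation status are the sociodemographic examples. Neither self-efficacy at T0 nor the role of T0 in the model (response, covariate or unused) is mentioned. Variables with a standardised difference above 0.1 are flagged and taken up in sensitivity analyses.

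**Costs.** In Tables 2 and 3 the row "Disease-related costs" has four marks, at weeks 4, 9, 14 and 24. There is none at week 0.

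**The concern.** The groups come from different sources: hospital EME programmes on one side, a self-registered online register on the other. In such a comparison the baseline value of the outcome is usually among the strongest measured confounders. Matching cannot balance it under the present schedule, so the regression is the only place to control it, and there it is neither named nor given a role. The balance check does not close the gap, because an imbalance found at T0 would lead only to a sensitivity analysis and leave the primary estimate unchanged.

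At stake are the size of the T2 effect and, since the bias changes sign with the unstated model form, its direction.

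For costs the problem lies in data collection. Prior care use and prior productivity loss may differ between hospital patients and register volunteers. A later analysis plan cannot recover a baseline value that nobody collected.

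**Working it through.** **Step 1: the plan's own figure.** The plan states that "the estimated sample size to detect a difference of 1.5 points with 90% power (0.05 alpha) is 122 persons", with the attrition allowance worded as "Including a follow-up rate of 24% at T2". Two-sided alpha is assumed, since sidedness is not stated, and the 24% is read as loss, since only that reading gives 122.

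- n per arm = 2 × (1.960 + 1.282)² × 2.2² / 1.5² = 45.2, rounded up to 46.
- 46 / 0.76 = 60.5, rounded up to 61 per arm, total 122. The figure reproduces.
- It is an unadjusted T2 comparison with no baseline correlation in it.

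**Step 2: bias from a baseline gap.** Let *gap* be the T0 self-efficacy difference (EME minus control) that remains after matching and the named covariates, and *rho* the T0-T2 correlation. Neither is given, so both are assumed. Take equal SDs of 2.2 and suppose that, given T0, untreated T2 means are equal in the two groups.

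- T2 contrast without T0 adjustment: bias = rho × gap.
- Change from T0 (T0 as response, group-by-time contrast): bias = rho × gap - gap = -(1 - rho) × gap.
- T2 adjusted for T0 self-efficacy: bias about 0.

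For a gap of 0.25 SD = 0.25 × 2.2 = 0.55 points:

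| rho | T0 ignored | Change contrast |
|---|---|---|
| 0.3 | +0.165 (11% of 1.5) | -0.385 (26%) |
| 0.5 | +0.275 (18%) | -0.275 (18%) |
| 0.7 | +0.385 (26%) | -0.165 (11%) |

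Signs reverse if the EME group starts lower.

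**Step 3: consequence at rho = 0.5 and 46 analysed per arm.** SE = 2.2 × √(2/46) = 0.459.

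- T0 ignored: 0.275 / 0.459 = 0.60. Two-sided type I error = Φ(-1.96 + 0.60) + Φ(-1.96 - 0.60) = 0.087 + 0.005, about 9%.
- Change contrast: at rho = 0.5 the SD of change is 2.2 × √(2 × 0.5) = 2.2, so the SE is the same. A true 1.5 is estimated as 1.225 on average, and power is Φ(1.225 / 0.459 - 1.96) = Φ(0.71), about 76%.

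**Step 4: simulation check.** With a true effect of 0, a gap of 0.3 SD (0.66 points), rho 0.5, 46 per arm and 100 runs, the mean estimates were +0.35 for T2 unadjusted, -0.31 for the change contrast and +0.02 for T2 adjusted for T0 (Monte Carlo SE 0.04 to 0.05). Theory gives +0.33, -0.33 and 0. Keeping T0 as a response but reading off the T2 group difference also gave +0.35.

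**Step 5: how often the balance flag fires.** Even with perfect balance in expectation, the standardised difference has SE √(2/n). P(|d| > 0.1) = 2 × [1 - Φ(0.1 / √(2/n))] = 0.58 at 61 per arm and 0.63 at 46. A flag is therefore likely for any one variable, and sensitivity analyses alone are a weak response.

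**Step 6: effect of adjustment on precision.** The residual SD is 2.2 × √(1 - rho²), or 1.905 at rho = 0.5. Power at 46 per arm for 1.5 points is then 96.5%, against 90.5% unadjusted (normal approximation). Adjustment does not raise the required N.

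**Step 7: costs.** The documents give no cost figures, so no bias in francs can be calculated. The finding rests on the schedule in Tables 2 and 3.

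**The case against.** The covariate lists are open examples and the full protocol or analysis plan is not shown, so baseline self-efficacy is unnamed rather than excluded. T0 is collected in both arms and the model is a repeated-measures one, so T0 may already have a role. This is fair, and it rules out any claim that the plan leaves baseline self-efficacy out. What stands is that the permissible readings give biases of opposite sign, and that the article names fatigue impact but not the baseline of the outcome on which it is powered.

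Some stronger readings are tempting but unsupported:

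- *A baseline gap passes in full into the T2 effect.* Only the fraction rho does, and under a change contrast the bias has the opposite sign.
- *The T0 MFIS is used twice, as covariate and response.* That follows only if the fatigue-impact covariate is the T0 MFIS score and T0 is also a response. The article says neither, and it would concern the MFIS model alone.
- *The study is underpowered.* The 122 reproduces without adjustment, so the precision gain is a bonus.
- *The matching covariates might be dropped from the model.* The plan already retains them.
- *The cost bias has a known size.* It has none in these documents.

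The plan also has simulated bias and E-value analyses. These address unmeasured confounding and do not replace adjustment for a measured baseline. On costs, occupation status is a partial proxy for productivity loss, and the questionnaire is said to cover changes in costs. Its items and recall periods are not shown, so some pre-study reference may exist, but no T0 measure is scheduled.

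**Conclusion.** The concern holds in limited form. The article does not say how T0 self-efficacy enters the T2 contrast, and matching cannot balance it. For an assumed residual gap of 0.25 SD and rho from 0.3 to 0.7, the T2 difference would be off by 0.17 to 0.39 points in either direction; at rho = 0.5 it is +0.28 or -0.28, 18% of the target difference. The gap and rho are assumptions, and no actual gap is known.

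The change-contrast figure also depends on untreated T2 means being equal given T0. If the groups instead followed parallel paths, the change contrast would be the unbiased one. That is a further reason to settle and justify the choice before analysis.

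The cost point is firmer as to fact, because the schedule is stated, but its size cannot be determined. Pre-existing cost differences cannot be adjusted for directly, and occupation status does not capture prior care use.

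**What to change.** **Outcomes.** In the primary model for SEPECSA, MFIS, OSA and SF-12, use T1, T2 and T3 as responses, with group, visit and group-by-visit terms. Enter the T0 value of the same outcome, with its visit interaction, as a fixed covariate, so that T0 is not also a response. State that the primary estimate is the adjusted group difference at T2. This costs nothing: the T0 data are already collected, and analysis is due to begin only at the end of 2025.

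**Costs.** Give the existing cost questionnaire at T0 to participants of both groups still to enrol, and a short retrospective version to those already past T0. Use the baseline value as a covariate in the cost model, with occupation status as a supplementary proxy. State the incomplete baseline cost data as a limitation. The price is one more form for fatigued participants and recall error among those asked late. At least the first 15 matched pairs (December 2024) may need the recall version, so collection will not be uniform.
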